#### Symptomatology

The identification of specific depressive symptoms will be considered as a secondary objective. The presence of male-specific depressive symptoms will be recorded using the Gotland Scale for Male Depression [18, 49], which is the only screening instrument currently available for detecting masked male depression. A validation study by Zierau et al. (2002) found an internal consistency of Cronbachs α = 0.86 for the overall scale, 0.75 for the depression subscale and 0.78 for the stress subscale. With regard to convergent validity, high correlations were observed with the conventionally used Major Depression Inventory (Spearman’s ρ = 0.77) and the WHO-5 (ρ = − 0.69) [18].

#### Risk factors

To identify risk factors of PPD, various secondary objectives will be evaluated. The course of disease was chosen as a secondary objective, as numerous studies have demonstrated its moderating influence on the development of depressive symptoms. The course of disease is not recorded in the PHQ-9 and will therefore be assessed using additional items regarding the duration of the current episode and previous episodes.

To detect present anxiety symptoms, the Adult Separation Anxiety Questionnaire (ASA-27, [50]) and the Anxiety Sensitivity Index (ASI, [51]) will be administered. The ASA-27 assesses symptoms of separation anxiety in adulthood. Principal components analysis of the ASA-27 revealed a coherent construct of separation anxiety with high internal consistency (Cronbach’s alpha = .95) and high retest reliability (r = .86; *P* < .001) [50]. The ASI questionnaire measures individuals’ tendency to interpret anxiety-associated physical sensations as threatening. It has an internal consistency of .88 (Cronbach’s alpha) and .85 (Guttman split-half reliability). Furthermore, the ASI is factorially independent of other anxiety measures [52].

Global assessments of the subjective judgment of the child’s and of the mother’s health status as possible influencing variables will be recorded using self-constructed items. Additionally, it will be asked whether a diagnosis of maternal postpartum depression is present.

The normative gender role orientation of the study participants will be evaluated using the Questionnaire of Normative Gender Role Attitudes (NGRO [44];). The NGRO focuses on internalized, personal gender role models and locates respondents between the poles of traditional vs. egalitarian standard expression. The internal consistency of the 29 items version of the NGRO is high (Cronbach’s alpha = .91). The calculation of the retest reliability gave a coefficient of r = .76 [44].

Social support will be measured using the standardized German short form of the Social Support Questionnaire (F-SozU-K-14 [45];), a unidimensional scale assessing support as perceived or anticipated support, with a focus on emotional and practical support and social integration. Additionally, the use of support systems (e.g. support from grandparents, infant care facilities, etc.) will be examined using self-constructed items.

Concerning pregnancy and birth, it is relevant to record whether the pregnancy was planned, unplanned or unwanted, whether artificial insemination was used and whether the birth was premature or involved multiple births. Furthermore, perinatal variables such as caesarean section delivery will be collected. The father should also indicate whether or not he is the child’s biological father.

The involvement of the father in the child’s care will be assessed using self-constructed items. These items cover, for example, the nighttime care, the inclusion and effectiveness of the father in the child’s upbringing and the use of paternity leave. The extent of perceived self-efficacy will be assessed using the General Self-Efficacy Scale (GSE, [53]), which covers expectations of competences e.g. a person’s subjective belief that he/she will be able to successfully deal with critical events.

The socio-demographic data collection will be based on the recommendations for epidemiological studies [54] as well as the study on Adult Health in Germany (DEGS [55];) with the objective of capturing risk factors (age, marital status, etc.). The migration background will be recorded according to the minimum indicator set for recording migration status [56]. In addition, the living conditions of young families will be assessed, including relationship status, childcare facilities, housing situation, and number and age of children.

#### Healthcare utilization

The utilization of medical services will be assessed based on scales of the health questionnaire of the study on Adult Health in Germany (DEGS [55]), the German version of the Client Sociodemographic and Service Receipt Inventory (CSSRI-D [57, 58];) and the questionnaire for the collection of health-related resource use in the elderly population (FIMA [59];). In addition, the use of health-related offers in the obstetric setting and the use of child-related health offers will be recorded.

### Statistical methods

#### Dealing with dropouts (unit missing)

Based on the data of the residents’ registration offices, it will be possible to describe differences in the composition of the population and the respondents of the two samples (fathers of an infant and control group) in terms of marital status, nationality, and age. The influence of these covariates on the response behavior can be controlled using logistic regressions. If there are significant differences between the population and the respondents of the two samples, a statistical adjustment of these differences will be made in the evaluation.

#### Dealing with missing values (item missing)

In psychometrically tested instruments, missing values are handled according to the instructions in the respective manual. If there are no recommendations, up to 30% of the missing data is replaced by the expectation-maximization algorithm method [60].

#### Analyses

Relative frequencies will be calculated for nominal-scaled variables. For ordinal-scaled and non-normally distributed interval-scaled measurements, the median is used as the preferred measure of central tendency. For interval-scaled variables, the arithmetic mean and standard deviations will be calculated. The choice of the respective statistical method for group comparisons depends on the scale level of the dependent variable. Although a matched sampling will be performed, this information cannot be used in the evaluation due to the anonymity of the survey. The evaluation therefore requires the use of independent samples techniques. Nominal distributions will be compared using Chi-square and Fisher’s exact tests. Parametric tests (t-test, analysis of variance) will be used for interval-scaled measurements. The effect of socio-demographic and other influencing factors will be calculated using logistic regressions.

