## Objectives

The aim of our study is to examine the prevalence of PPD in fathers within the first year after childbirth compared to the prevalence of depressive symptoms in a matched sample of men without recent paternity. We hypothesize that the prevalence of PPD in fathers within one year after childbirth is higher than the prevalence of depressive symptoms in a matched sample of men without recent childbirth. As one of the secondary objectives, we take a closer look at the group of fathers within one year after childbirth to assess differences in PPD prevalence in different time periods. Other secondary objectives are to identify specific symptoms and risk factors of PPD. Furthermore, service utilization regarding PPD is considered as a secondary objective on a healthcare level. In an exploratory add-on study, genetic and epigenetic mechanisms of PPD will be explored.

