
**Table 1 Tab1:** Objectives and measurements for each group

Objective	Instrument or self-constructed item	No. of items	Group
*Primary objective*			
Depressive symptoms	Patient Health Questionnaire (PHQ-9)	9	both
*Secondary objectives*			
Prevalence differences in different time periods	Date of birth of the child, date on which the questionnaire was filled out	2	fathers of an infant
Specific depressive symptoms	Gotland Male Depression Scale	13	both
Course of depression	regarding the presence and duration of the current episode and previous episodes	5	both
Symptoms of separation anxiety	Adult Separation Anxiety Questionnaire (ASA-27)	27	both
Individuals’ tendency to interpret anxiety-associated physical sensations as threatening	Anxiety Sensitivity Index (ASI)	16	both
Participants’ subjective judgment on their own health status	“How would you describe your health in general?”	1	both
Participants’ subjective judgment on the child’s and the mother’s health status	“How would you describe the health of your infant in general?” “How would you describe the health of the child’s mother in general?”	2	fathers of an infant
Diagnosis of maternal postpartum depression	“Has a doctor or psychotherapist diagnosed postpartum depression in the child’s mother?”	1	fathers of an infant
Extent of perceived self-efficacy	General Self-Efficacy scale (GSE)	10	both
Normative Gender Role Orientation	Questionnaire of Normative Gender Role Attitudes (NGRO)	29	both
Social support	Social Support Questionnaire (F-SozU-K-14)	14	both
Use of support systems	Are you supported by other people or support systems in the care of the newborn?	1	fathers of an infant
Pregnancy and birth	child’s biological father or not; pregnancy was planned, unplanned or unwanted: whether artificial insemination was used or not; complication during pregnancy or birth; premature, miscarriage, or involved multiple births; caesarean section delivery or natural birth; having other children	10	fathers of an infant
Involvement of the father	living in the same household as the infant during pregnancy and after birth; being a single parent; present at the birth; being involved in birth preparation; nighttime care; sleep quality because of the infant; daily time with the infant; use of paternity leave	10	fathers of an infant
Sleep quality in general	“How would you rate your sleep quality in general?”	1	both

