A potential limitation lies in the method of recruitment, which could produce a selection bias in the sample and thus restrict the external validity of the results. A further limitation is that study participants have to self-administer a high number of measurement instruments. This might hinder the feasibility of the trial and reduce the response rate. We have tried to address this issue by naming a contact person from the study team in case of questions, by giving examples on how to answer the questionnaire, and by reducing the questionnaire to relevant aspects. As we will also assess the general health status and other diagnoses such as anxiety, it will be possible to detect some of the potential confounding factors.

Our study will provide insights into the issue of PPD in fathers. Currently, there is no study on PPD using a matched control group. Studies conducted to date compared their results with historical control data, which carries the risk of over- or underestimation of the relative frequency of depressive symptoms after childbirth. A simultaneous detection of depressive symptoms, of symptomatology, and of risk factors using the same instruments will enhance the comparability of the results and thus ensure the scientific quality of the concluding statements. Surveying the healthcare situation will provide opportunities for the practice-oriented design of current care and thus information on the development of screening methods and healthcare concepts. Based on the findings of our study, further studies should address the standardization of measurement methods to identify PPD as well as male-specific healthcare interventions in fathers.

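### The group comparisons named for interval scores cannot, on the Gotland scale, tell a different symptom profile from a larger amount of depression

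*Protocol article*

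**What the plan says.** The Objectives section of the protocol article states: "Other secondary objectives are to identify specific symptoms and risk factors of PPD". The Symptomatology section repeats the aim: "The identification of specific depressive symptoms will be considered as a secondary objective". Table 1 assigns the 13-item Gotland Male Depression Scale to both groups. The Background names, as a gap in earlier research, the missing comparison of fathers' symptomatology with a matched control group on the same instruments, and the Discussion presents closing that gap as a strength. The Abstract expects the findings to inform screening instruments specific to paternal depression.

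On method, the Analyses section gives a selection rule: "The choice of the respective statistical method for group comparisons depends on the scale level of the dependent variable". For interval scores it continues: "Parametric tests (t-test, analysis of variance) will be used for interval-scaled measurements". Its only regression is a logistic one for socio-demographic and other influencing factors. The adjustment described for non-response covers marital status, nationality and age.

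On the scale itself, the Symptomatology section reports that "high correlations were observed with the conventionally used Major Depression Inventory", with Spearman's ρ = 0.77.

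**The concern.** Specific symptoms are a matter of profile: at a given level of depression, do new fathers report other symptoms than other men? A t-test of Gotland scores between all fathers and all controls has a different null, namely equal mean scores. The scale tracks depression closely by the protocol's own figure, and the primary hypothesis is that fathers have more depression. If that hypothesis is true, equal mean scores are not to be expected even when depressed fathers and depressed controls have exactly the same symptoms.

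A significant Gotland difference could then be the primary finding seen through a second instrument, while being available as evidence for the design of screening tools. In the other direction, a profile in which male-specific symptoms are relatively milder in fathers could be masked by the excess of depression.

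**Working it through.** **Inputs from the protocol (Sample size calculation).** 9200 men contacted in two equal groups; about 75% dropout; prevalence 8.0% in fathers and 5.0% in controls; significance level 0.05, taken here as two-sided.

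**The plan's own figure.** 0.25 × 9200 = 2300 respondents, so 1150 per group. The stated requirement of 2300 is reproduced within 3% by a two-sided two-proportion formula with continuity correction (1125 per group, 2250 in total).

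**Inputs assumed.** The protocol gives no Gotland SD, no gap between cases and non-cases, and no Gotland–PHQ-9 correlation. The gap D is taken as 1 to 3 SD and the correlation r as 0.3 to 0.77; the upper value is the protocol's coefficient against a different depression scale.

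**Question.** How often does the plain t-test reject when the symptom profile is identical and only the amount of depression differs? The standard error of a standardised mean difference is √(2/1150) = 0.0417. With z = difference/0.0417, the rejection probability is Φ(z − 1.96) + Φ(−z − 1.96).

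**Model A: only the share of cases differs.** Raw difference = (0.08 − 0.05) × D. SD = √(1 + v·D²), where v = (0.05 × 0.95 + 0.08 × 0.92)/2 = 0.0606.

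| D | Raw difference | SD | Standardised | z | Rejects |
|---|---|---|---|---|---|
| 1 | 0.03 | 1.030 | 0.029 | 0.70 | 11% |
| 2 | 0.06 | 1.115 | 0.054 | 1.29 | 25% |
| 3 | 0.09 | 1.243 | 0.072 | 1.74 | 41% |

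**Model B: the whole severity distribution shifts.** Moving prevalence from 5.0% to 8.0% at a fixed threshold needs a shift of 1.645 − 1.405 = 0.240 SD. The Gotland difference is r × 0.240.

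| r | Difference | z | Rejects |
|---|---|---|---|
| 0.3 | 0.072 | 1.72 | 41% |
| 0.5 | 0.120 | 2.87 | 82% |
| 0.77 | 0.185 | 4.43 | 99% |

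**Control rate of 5.3%.** The same section also cites 5.3% for controls. With it, Model A gives 10%, 21% and 34% (D = 1, 2, 3), and Model B gives 72% and 97% (r = 0.5, 0.77).

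**What conditioning on PHQ-9 achieves.** In Model B with an error-free PHQ-9, the group coefficient has expectation zero and the test rejects in about 5%. With PHQ-9 reliability R (assumed 0.80–0.90) and observed Gotland–PHQ-9 correlation r, the residual bias is (r/√R) × 0.240 × (1 − R), and the standard error is about √(1 − r²) × 0.0417.

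| r | R | Bias | SE | z | Rejects |
|---|---|---|---|---|---|
| 0.5 | 0.90 | 0.0126 | 0.0361 | 0.35 | 6% |
| 0.5 | 0.80 | 0.0268 | 0.0361 | 0.74 | 12% |
| 0.77 | 0.90 | 0.0195 | 0.0266 | 0.73 | 11% |
| 0.77 | 0.80 | 0.0413 | 0.0266 | 1.55 | 34% |

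The unadjusted rates for the same two correlations are 82% and 99%.

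**Contrast among PHQ-9-positive men.** Expected numbers are 1150 × 0.08 = 92 fathers and 1150 × 0.05 = 57.5, about 58, controls. SE = √(1/92 + 1/58) = 0.168. The difference detectable with 80% power is (1.960 + 0.842) × 0.168 = 0.47 SD; power is 43% at 0.3 SD and 66% at 0.4 SD.

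**The case against.** The Analyses section is a general rule for all interval-scaled variables. It does not mention the Gotland scale, say whether all respondents or only PHQ-9-positive men are compared, or say whether totals or items are used. An analysis of variance could carry PHQ-9 status as a second factor. The article condenses a fuller plan that may settle this. All of that is fair: a reader might infer that the protocol explicitly commits to an unconditional Gotland t-test, and it does not. What stands is that the protocol does fix a selection rule, scale level, and that this rule, applied to the comparison which the Background and Table 1 describe, leads to an unconditional test.

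A reader might also infer that a Gotland difference is bound to be reported as specific to paternal depression. The document contains no rule of interpretation, so the most that can be said is that a difference could be read that way.

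A third tempting reading is that the prevalence excess alone makes a spurious result near certain. It does not. Under Model A, non-rejection is the likelier outcome throughout (59–89%). The highest rates need a shift of the whole distribution, which the protocol does not state.

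Finally, the objective may be meant more loosely, as a description of fathers' symptoms beside those of controls. An overall comparison does serve that purpose, but as a measure of symptom load; it does not identify specific symptoms.

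**Conclusion.** The point holds as a limitation of the methods named: choosing tests by scale level gives nothing that separates symptom profile from amount of depression, so a significant Gotland difference could largely restate the primary prevalence result. With identical profiles and 1150 respondents per group, the plain test rejects in about 11–41% of trials (Model A) or about 41–99% (Model B). Every scenario at the planning rates is at least twice the nominal 5%.

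The width of that range reflects assumptions about how the excess arises, how far cases lie from non-cases, and how closely the Gotland score follows severity. The direction of the problem does not depend on them, provided that fathers do have more depression. The change is worth making, but it concerns a secondary objective and leaves the primary comparison untouched.

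**What to change.** For the symptomatology objective:

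- Compare Gotland total, subscale and item scores between groups conditional on PHQ-9 severity: a regression on group, PHQ-9 score and their interaction (logistic or ordinal for items), reported with 95% confidence intervals.
- Add a sensitivity analysis over plausible values of PHQ-9 reliability. Read the adjusted result as supportive, not as the sole rule for calling a symptom specific.
- Report the same contrast among PHQ-9-positive men as a supporting estimate, and state its imprecision.
- Label the unadjusted Gotland difference as a difference in overall symptom load.

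The cost is analysis wording only. Table 1 shows that both instruments are collected in both groups, and the Trial status section says that analysis was still under way in August 2019. The downside is residual confounding by severity, which adjustment for an imperfectly measured PHQ-9 reduces but does not remove.

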As primary measure, the Patient Health Questionnaire (PHQ-9) will be used (for detailed descriptions of all instruments used in this study, see below and cf. Table 1). The PHQ-9 is a gender-independent instrument with good psychometric properties [43]. Instead of comparing the results regarding the prevalence of PPD in fathers within one year after childbirth to findings from other studies (historical controls), the data in our study will be compared to a matched sample of men without new paternity one year prior to the survey. This design allows comparative statements to be made, in which the comparison is estimated to be as unbiased as possible, thus increasing the scientific quality of the statements. Furthermore, the date of childbirth and the date of answering the questionnaire will be recorded. From these data, differences in the prevalence rates can be calculated for different time periods after the birth of the child. To assess male-specific symptoms in PPD, the survey will also include the Gotland Male Depression Scale [18]. Moreover, potential risk factors will be considered using various instruments, including the Normative Gender Role Orientation Questionnaire [44], the General Self-Efficacy Scale, and the Social Support Questionnaire [45], as well as self-constructed items (including, e.g., the child’s and mother’s perceived health status). Other potential risk factors include the presence of an earlier depressive episode, the presence of anxiety symptoms, circumstances of pregnancy and childbirth, childcare, as well as demographic factors such as age, marital status, and immigration background. The survey will also cover the healthcare situation and the utilization of obstetric services by fathers with PPD. To record healthcare utilization, the fathers will indicate which services they have used in general and with regard to mental health problems in particular during gestation and since the baby was born (based on different scales, see below and cf. Table 1). Based on the prevalence of PPD and information about healthcare utilization, it will be possible to calculate the rate of fathers who would use specific treatment. The healthcare providers which are commonly contacted during pregnancy and after childbirth (e.g., general practitioner, midwife as part of the aftercare, birth preparation courses) can be used to identify low-threshold service access to adequate healthcare and possibly show important starting points for the implementation of preventive measures or for early interventions in fathers with PPD who are currently under-served.

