
## Discussion

Our controlled cross-sectional epidemiological study aims to compare the prevalence of PPD in fathers within the first year after childbirth with the prevalence of depressive symptoms in a matched sample of men without new paternity. Furthermore, our study should reveal differences regarding the prevalence of PPD in fathers in different time periods within one year after childbirth. Additionally, potential male-specific symptoms and risk factors of PPD in fathers will be investigated. A further goal is to assess the current healthcare situation of fathers with PPD in Germany. Our findings will contribute to closing the above-mentioned research gaps and offer possibilities to refine healthcare options for fathers with PPD. Compared to previous studies, our study has several methodological strengths. A central advantage is the direct comparison of the prevalence of PPD in fathers of an infant with the prevalence of depressive symptoms in a matched group of men without recent paternity from the general population. The simultaneous detection of depressive symptoms using the same measurement instrument will minimize the risk of producing an estimation bias of the relative prevalence of PPD and thus increase the external validity of the results. The large sample size compared to previous studies will allow us to perform a variety of subgroup analyses. Furthermore, the large sample size and the recording of the date of childbirth and the date of responding to our questionnaire will allow us to examine prevalence differences for several time periods within one year after childbirth and to analyze specific symptoms of PPD and risk factors. A further advantage of our study lies in the consideration of the healthcare situation of fathers with PPD in Germany – an issue that has not been considered in the research so far. By examining these aspects, low-threshold service access can be revealed, enabling important hints to be derived for the development of adequate care options for fathers with PPD. The identification of risk factors for the development of PPD in fathers will allow an early and specific treatment for these men through the utilization of adequate healthcare offers. Finally, genetic and epigenetic risk patterns of PPD to be identified in the exploratory add-on study might serve as future biomarkers for early interventions or even personalized preventive measures in men at risk of PPD.

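### The only stated rule for comparing interval-scaled scores is an unadjusted t-test or ANOVA; applied to the Gotland scale, it cannot separate a different symptom picture in fathers from more depression

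*Protocol article*

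**What the plan says.** - **Objective.** The Objectives section states: "Other secondary objectives are to identify specific symptoms and risk factors of PPD". The Discussion expects the sample "to analyze specific symptoms of PPD and risk factors".
- **Instrument.** Study design: "To assess male-specific symptoms in PPD, the survey will also include the Gotland Male Depression Scale". Symptomatology: "The presence of male-specific depressive symptoms will be recorded using the Gotland Scale for Male Depression". Table 1 lists the scale (13 items) under specific depressive symptoms, for both groups.
- **Contrast.** The Background faults existing work for not setting fathers' symptomatology against a matched control group measured with the same instruments. The closing part of the Discussion counts simultaneous measurement of symptomatology among the study's strengths. The comparison argued for is fathers versus controls, though no sentence defines it for the Gotland scale.
- **Method.** Analyses: "The choice of the respective statistical method for group comparisons depends on the scale level of the dependent variable". For scores: "Parametric tests (t-test, analysis of variance) will be used for interval-scaled measurements". Independent-samples techniques are prescribed because the matching cannot be used. The one regression named is: "The effect of socio-demographic and other influencing factors will be calculated using logistic regressions".
- **Overlap with general depression.** Symptomatology reports that "high correlations were observed with the conventionally used Major Depression Inventory", with a Spearman coefficient of 0.77, and that the scale has a depression subscale and a stress subscale.
- **Expected direction.** The Objectives hypothesise a higher prevalence of depressive symptoms in fathers. Sample size calculation plans on 8.0% against 5.0%, after giving 5.3% as the control prevalence.

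**The concern.** A symptom is specific to PPD if depressed fathers show it more than equally depressed men without a newborn. A difference in mean Gotland score between all fathers and all controls does not address that. If fathers are more depressed on average, as hypothesised, their expected Gotland score is higher even when the symptom picture at any given severity is the same in both groups. This is a problem of identification and holds whatever the p-value.

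It matters because the Abstract says the findings should inform PPD-specific screening instruments, and the Background bases the need for them on PPD having distinct symptoms. Under the stated rule, a real difference in the primary outcome by itself pushes the symptom comparison towards a positive result, so the two findings would not be separate evidence.

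**Working it through.** **Inputs from the article.** Prevalence 8.0% against 5.0% (or 5.3%); total sample 2300; 9200 men contacted with about 75% dropout; Gotland correlation 0.77.

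**Assumptions.** Equal split of respondents; two-sided 5% test; standardised scores; the 0.77 (a Spearman coefficient with a different inventory) used as a linear correlation with severity and varied from 0.5 to 0.86; no specific symptom effect at all.

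**1. The article's sample size.** With mean prevalence 0.065:

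n per group = [1.96·√(2·0.065·0.935) + 0.842·√(0.08·0.92 + 0.05·0.95)]² / 0.03² = 1059, or 2118 in total. With continuity correction it is 1125, or 2250 in total, about 2% below the stated 2300. Also 9200 × 0.25 = 2300, so 1150 per group, where power is 83.1%. The figure reproduces, and 1150 per group is used below.

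**2. Standard error of a difference in standardised means.** √(2/1150) = 0.0417. The chance of a significant difference towards fathers is Φ(difference/0.0417 − 1.96).

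**3. Model A: the whole severity distribution shifts.** Severity is normal with a fixed cut-off.

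- From 5.0% to 8.0%: shift = z(0.95) − z(0.92) = 0.240 SD. Gotland difference = 0.77 × 0.240 = 0.185 SD. 0.185/0.0417 = 4.43, so Φ(2.47) = 99%.
- From 5.3% to 8.0%: shift 0.211 SD; Gotland difference 0.163 SD; ratio 3.90; Φ(1.94) = 97%.

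| Correlation | 5.0% controls | 5.3% controls |
|---|---|---|
| 0.50 | 0.120 SD, 82% | 0.106 SD, 72% |
| 0.69 | 0.165 SD, 98% | 0.146 SD, 94% |
| 0.77 | 0.185 SD, 99% | 0.163 SD, 97% |
| 0.86 | 0.206 SD, 99.9% | 0.182 SD, 99% |

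**4. Model B: only the share of cases rises by 3 points.** Cases lie D within-group SDs above non-cases on the Gotland scale. Standardised difference = 0.03·D / √(1 + D²·0.065·0.935).

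- D = 1: 0.029 SD, chance 10%.
- D = 2: 0.054 SD, chance 25%.
- D = 3: 0.072 SD, chance 41%.

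**5. Does conditioning on severity help?** In 2000 simulated surveys under Model A (5.0% to 8.0%, correlation 0.77), the share of significant results was:

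| Analysis | Significant |
|---|---|
| Unadjusted t-test | 99% |
| Adjusted for true severity | 5.6% |
| Adjusted for severity measured with reliability 0.85 (assumed) | 15% |
| Only men above the cut-off | 5.8% |

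The 15% can be checked by hand. Adjustment leaves 0.77 × 0.240 × (1 − 0.85) = 0.028 SD. The residual SD is √(1 − 0.77²·0.85) = 0.704, so the standard error is 0.704 × 0.0417 = 0.029. The ratio is about 0.94, and Φ(0.94 − 1.96) is about 15%.

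**6. Precision among cases.** 0.08 × 1150 = 92 fathers and 0.05 × 1150 ≈ 58 controls. √(1/92 + 1/58) = 0.168 (in within-case SD units), and 0.168/0.0417 ≈ 4.0.

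**The case against.** The strongest objection is that this is missing detail. The Analyses rule is generic and does not name the Gotland scale. An article may leave the model for a secondary objective to a full protocol or analysis plan that is not shown. Specific symptoms of PPD could also mean a comparison among depressed men. ANOVA could carry PHQ-9 status as a second factor, the PHQ-9 can be scored categorically, and the two Gotland subscales would allow a profile comparison. A severity-conditional analysis is therefore neither planned nor excluded.

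Much of that stands and limits the point. A reader might infer that the plan commits to finding specific symptoms by a t-test on Gotland scores and to reporting a higher score as a PPD-specific picture. The article says neither. A reader might also infer that a significant difference must follow from more depression. Only the expected direction follows; significance depends on how the distribution changes, and under Model B it is the less likely result.

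The objection does not remove the point. The article itself presents symptomatology as a father-control comparison on common instruments. The rule it states for such comparisons is chosen by scale level alone. The only regression it names is for influencing factors, and its planned adjustment for non-response covers age, nationality and marital status. The stated rule is thus a poor fit for the stated objective.

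**Conclusion.** The point holds in a limited form. If the stated rule is applied to the Gotland score, overall severity and symptom profile are confounded, and a higher score in fathers could be read as specificity when it reflects only more depression. That conclusion needs only the reported correlation and the study's own hypothesis.

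The size is uncertain. With no specific symptom, the chance of a significant difference is about 72% to 99.9% under a whole-distribution shift and about 10% to 41% if only the share of cases rises, against a nominal 5%. These ranges rest on the assumed severity models, the equal split, and the use of a rank correlation with another inventory as a linear one. The primary prevalence comparison is unaffected.

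**What to change.** State in the analysis section that:

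1. Symptom specificity is judged from the father-control difference in Gotland items and the depression and stress subscales, conditional on the PHQ-9 score.
2. A supporting comparison is made among PHQ-9-positive men of both groups.
3. The plain t-test on the Gotland score is reported as a comparison of severity only.
4. Tests of the 13 items and two subscales are labelled exploratory or corrected for multiplicity.

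This changes analysis wording only. Both scales are collected in both groups, and Trial status describes the analysis as ongoing in August 2019.

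There are real downsides. PHQ-9 measurement error leaves residual confounding (about 15% false positives at an assumed reliability of 0.85 under Model A), so a small adjusted difference should be read cautiously. The cases-only comparison has about 92 against 58 men and a standard error about four times larger, so it can support the main analysis but not replace it.
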